### Qualification of practitioners

Only licensed TC coaches with more than 10 years of teaching experience will perform TC training. Each coach will receive additional human subject protection training a week before the TC training begins. Furthermore, each intervention group will be assigned a registered nurse with at least 3 years of clinical experience to avoid serious adverse events. Every participant will be guided in standardised operating procedures before study initiation to further clarify the protocol trial, flow chart and individual responsibilities.

### Study intervention

#### Experimental group: TC training

The trial protocol will be administered at the Sports Centre of Changsha First Social Institute. A total of 284 eligible participants will be randomly divided into four groups. Amongst these, three groups (group 1, group 2 and group 3) will undergo TC training with different frequencies (one, three or five sessions/week, 60 min/session, sustain for 12 weeks). Before the training begins, each group will be assigned a coach. The participants will be familiarised with the TC programme, including principles, practice strategies and safety considerations, through printed materials and short videos a week prior to study initiation. Three research assistants will supervise and guide the participants’ learning conditions through weekly phone calls.

At the beginning of this study, participants of three TC groups will commence the interventions at the same time under the guidance and supervision of coaches to prevent seasonal changes in disease severity. Group 1 will practice Chen-style TC one time a week for 12 weeks under the guidance of a coach with 10 years of teaching experience. The TC training programme shall be jointly formulated by the research group members and coaches after discussion. See Figs. 2 and 3 for the movements included in TC. The whole training process includes 10 min of warm-up, 40 min of TC training and 10 min of cooling down. The details are shown in Additional file 1. Sessions for the first week are designed to enable participants to master each training movement, breathing technique and relaxation method under the guidance of the instructors. The remaining sessions will consist of the following sections: (1) warming-up and review of TC principles and techniques; (2) Chen-style TC with 16 forms for two times; (3) breathing mechanics and (4) cooling down. Meanwhile, video recordings will be used to monitor the quality of TC training and offer feedback to coaches on time throughout the study. For group 2 and group 3, the parameters will be in line with group 1, except that training frequency will be transferred to 3 times a week and 5 times a week, respectively.

**Fig. 2 Fig2:**
[figure not shown]
Sixteen-form Chen-style Tai Chi. Notes: **A** Commencing Form. **B** Buddha’s Warrior Attendant Pounds Mortar. **C** Tuck in Robes. **D** Single Whip. **E** Wave Hands Like Clouds. **F** Double Push Palms. **G** Step Back and Whirl Arms on Both Sides. **H** White Crane Spreads Wings

**Fig. 3 Fig3:**
[figure not shown]
Sixteen-form Chen-style Tai Chi. Notes: **I** Diagonal line spread step. **J** Deflect through The Back. **K** the Chopping Hand. **L** Strike Fist. **M** Six Seals and Four Closings. **N** Single Whip and Body Defending Punches. **O** Turn-back and Buddha’s Warrior Attendant Pounds Mortar. **P** Closing Form (mode: [name])

#### Control group: health education

The control group will keep their daily lifestyle and will not receive any rehabilitation treatment during the intervention, except for one health lecture per week for 12 weeks.

#### Permitted and prohibited concomitant treatments

Participants should avoid performing any regular physical exercise based on the Centres for Disease Control and Prevention guideline (https://www.cdc.gov/physicalactivity/basics/older_adults/index.htm), except TC training, throughout the course of this protocol trial. Besides, participants still can maintain their regular drug treatments for some diseases (e.g. diabetes, heart disease and hypertension), but painkillers, such as opioids, non-steroidal anti-inflammatory drugs and antidepressants, will be banned. Any changes in drug usage throughout the intervention period will be recorded.

### Outcomes

Primary and secondary outcomes will be evaluated at baseline, immediately after finishing the TC training (week 12) and at the end of the follow-up period (week 24). In addition, primary outcome (the changes of LBP intensity at rest) will also be collected every week 4 and week 8 after the intervention started. All indicators will be selected in assessing outcomes for estimating treatment success for CLBP [36–38], concentrating on pain intensity, psychology, QOL and functioning disability.

#### Baseline characteristics of trial participants

The socio-demographic information that will be collected includes gender, age, body mass index, marital status, living status, working status and education level. The clinical and CNLBP-related information that will be collected includes LBP duration, self-reported comorbidities, drug use condition (type, frequency and duration) before the start of this trial and history of back surgery.

#### Primary outcome

The primary outcome (the changes of LBP intensity at rest) will be measured using the VAS [39, 40], a horizontal line of 0–10 cm long, scores of 0 and 10 are at the extremes of the two scales, representing the pain status: “no pain” and “worst imaginable pain,” respectively. Participants will be asked to put a mark on the VAS scale to show how severities of their LBP have been over the past 24 h [39]. The higher the VAS score, the greater the pain intensity. Such has confirmed its sensitivity and reliability for patients with LBP [41]. The outcome will be collected at baseline before randomisation and immediately after the completion of week 4, week 8, week 12 of the intervention and the end of follow-up.

#### Secondary outcomes

The comorbidities of CNLBP will be considered to avoid the effect of confounding factors on outcome indicators. For secondary outcomes, we will collect a wide range of variables, including psychology (Beck Depression Inventory-II [BDI-II], Pain Catastrophising Scale [PCS] and Five Facet Mindfulness Questionnaire [FFMQ]), functional disability (Oswestry Disability Index [ODI]) and QOL (Short Form-36 [SF-36]) as follows:BDI-II: BDI-II contains 21 items and is widely used to measure the severity of depression symptoms. A higher BDI-II score indicates a greater degree of depression. Its Chinese version has been proven to have good reliability and validity [42].PCS: PCS is used to describe pain catastrophising. It consists of three subscales with 13 items: rumination, magnification and helplessness. Each item is scored from 0 (never) to 4 (always). A higher score represents a higher level of pain catastrophising [43]. The psychometric properties of the Chinese version of PCS are satisfactory and have good reliability and validity [44].FFMQ: This scale is applied to measure five aspects of mindfulness: observe, describe, act aware, nonjudge and nonerect. The questionnaire contains 39 items; each item is scored on a scale of 1 to 5; a higher score indicates a higher level of mindfulness [45]. The Chinese version of the FFMQ has acceptable psychometric properties and is a valid instrument for the assessment of mindfulness [46].SF-36: This scale evaluates health-related QOL from eight aspects with 36 items (0–100), including physical functioning, role–physical, bodily pain, general health, vitality, social functioning, role–emotional, mental health and health transition. A higher score indicates a greater health status [47].ODI: This scale assesses disability in patients with LBP on 10 dimensions, including pain intensity, personal care, lifting, walking, sitting, standing, sleeping, sexual activity (if applicable), social life and travelling. Each dimension has six levels. A score of 0 was used for the minimum disability level; five points were used for the highest degree of disability. The Chinese version of the ODI is responsive and appropriate for usage in patients with CLBP after conservative therapy [48].

### Adherence

The electronic data management platform Yiducloud will be set by us to regularly automatically release daily tasks to participants via WeChat. A research assistant will be responsible to ensure that each participant is informed. The contents of the notice include the following aspects:Training plan for the next day;Reminders to avoid performing a new regular exercise programme except the TC training and maintain their usual physical activities as much as possible;Monitoring sign-in and recording medicine changes timely.

In addition, the research assistant will also be responsible for monitoring the participants’ attendance and filling out the class sign-in sheets for each in-person lesson, which will be used to track the participants’ attendance.

### Safety evaluation

Regardless of the reason for withdrawal during the process of intervention and follow-up period, we will figure out and detailed record the reasons for the withdrawal of participants in the case report forms (CRFs). If the participants experience any adverse events (AEs, defined as any impairment caused by TC training), the nurses will handle the AEs at once and contact the relevant research assistant. The details of AEs, including the time of occurrence, duration, degree of symptoms and treatment measures, will be recorded by the assistant in CRFs.

The doctor will provide comprehensive consideration to evaluate their correlation with clinical intervention training, who will advise whether the participant could continue to participate in the following study and give any medical treatment to relieve uncomfortable symptoms. Meanwhile, such events will be reported by the Ethics Committee. Then, the assistant in CRFs will calculate and record the incidence of adverse events via the following formula: Incidence of AEs (%) = (sessions with AEs / total exercise sessions in this group) × 100%, to measure the safety concerns. In addition, we will try to contact such participants and expect them to complete the follow-up.

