## Methods and analysis

### Trial design

This study is a single-centre, randomised, single-blinded (outcome assessors, data managers and the statistician), parallel controlled trial, which will be carried out in Changsha First Social Welfare Institute, Hunan Province, China. In total, 284 eligible participants with CNLBP will be randomly and equally divided into four groups in a 1:1:1:1 allocation ratio. Three experimental groups will undergo 12 weeks of supervised TC training and complete one, three or five TC sessions weekly, respectively. The control group will not receive any rehabilitation programme. Meanwhile, all participants will receive weekly health lectures until the end of the 12-week intervention and will be required to maintain a healthy lifestyle, afterwards followed by 12 weeks of follow-up after the end of the intervention.

The primary outcome (the changes of LBP intensity at rest) will be measured at baseline before randomisation and immediately after the completion of week 4, week 8, week 12 of the intervention and the end of follow-up (week 24). The secondary outcomes will be measured at baseline before randomisation and immediately after the completion of week 12 of the intervention and the end of follow-up (week 24). The details of the time schedule of this trial are shown in Table 1. The recommendations of the Consolidated Standards of Reporting Trials (CONSORT) will be strictly followed, and the protocol will be reported in line with the Standard Protocol Items (SPIRIT) [28] (Additional file 2). The flow chart is presented in Fig. 1.

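### The adverse-event route and per-session incidence described do not measure harm comparably across weekly frequencies and give no figure for control

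*Protocol article*

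**What the plan says.** Under Qualification of practitioners, "each intervention group will be assigned a registered nurse with at least 3 years of clinical experience to avoid serious adverse events". No nurse is named for the control group. Under Safety evaluation, when an event occurs "the nurses will handle the AEs at once and contact the relevant research assistant"; the assistant enters the details in the case report form and a doctor judges the relation to training. Two further statements in that section shape the result. The events in scope are "AEs, defined as any impairment caused by TC training". The measure for each group is "Incidence of AEs (%) = (sessions with AEs / total exercise sessions in this group) × 100".

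The training schedule is "one, three or five sessions/week, 60 min/session, sustain for 12 weeks". The control group "will not receive any rehabilitation treatment during the intervention, except for one health lecture per week for 12 weeks".

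Pain is assessed in all four arms at baseline and weeks 4, 8, 12 and 24 (Trial design; Primary outcome). Safety evaluation also has reasons for withdrawal recorded during both intervention and follow-up, without limiting this to the Tai Chi arms. The Statistical analysis section plans no between-arm test of harms.

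**The concern.** The staff through whom events are described as reaching the record are placed where the sessions are, and the number of sessions is what is randomised. A problem that starts and resolves between two sessions has less chance of being noted in the once-weekly arm than in the five-times-weekly arm. A problem in a control participant, or in any participant after week 12, has no described route unless it leads to withdrawal.

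The incidence formula adds a second dependence on frequency, because it divides by sessions. The trial is meant to inform the choice of weekly frequency (Introduction, Discussion), and how well each frequency is tolerated is part of that choice. A group incidence that changes with frequency for reasons other than harm, and that does not exist for control, could mislead a reader in either direction.

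**Working it through.** The protocol states no adverse-event rate or count, so there is no figure of its own to reproduce.

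**Step 1. Planned sessions.** Weekly frequency × 12 weeks gives 1 × 12 = 12, 3 × 12 = 36 and 5 × 12 = 60 per participant, and 0 in control. With 71 participants per group (Sample size) that is 852, 2556, 4260 and 0 participant-sessions. For control the formula is 0/0.

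**Step 2. Share of between-session events that is captured.** These assumptions are not in the protocol:
- The true weekly rate is the same in each arm.
- Onset is equally likely on each of the 7 days.
- An event is noted only if it is present on a session day.
- Sessions fall on Monday; Monday, Wednesday and Friday; or Monday to Friday.

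Captured share = number of the 7 onset days from which an event lasting *d* days meets a session day, divided by 7.

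| Duration | 1/week | 3/week | 5/week | Count ratio, 5 vs 1 |
|---|---|---|---|---|
| 1 day | 1/7 = 14% | 3/7 = 43% | 5/7 = 71% | 5.0 |
| 2 days | 2/7 = 29% | 6/7 = 86% | 6/7 = 86% | 3.0 |
| 3 days | 3/7 = 43% | 7/7 = 100% | 7/7 = 100% | 2.3 |
| 7 days | 100% | 100% | 100% | 1.0 |

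**Step 3. The protocol's measure.** Count each captured event once and divide the captured share by 1, 3 and 5 sessions per week.

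| Duration | 1/week | 3/week | 5/week | Incidence ratio, 5 vs 1 |
|---|---|---|---|---|
| 1 day | 0.143 | 0.143 | 0.143 | 1.0 |
| 2 days | 0.286 | 0.286 | 0.171 | 0.6 |
| 3 days | 0.429 | 0.333 | 0.200 | 0.47 |
| 7 days | 1.000 | 0.333 | 0.200 | 0.2 |

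If an event is instead counted at every session it overlaps, the mean number of overlaps is *d* × *f* / 7. Dividing by *f* leaves *d* / 7 in each arm, so the ratio is 1.0 throughout.

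**Step 4. A second model.** Assume 0.01 between-session events per week, reported at the next session if within a recall window *R*. The share detected is min(1, *R* / (7/*f*)).
- *R* = 1.4 days: 0.024, 0.072 and 0.12 detected events per participant; per-session incidence 0.20% in each arm.
- *R* = 7 days: 0.12 detected events per participant in each arm; per-session incidence 1.00%, 0.33% and 0.20%.

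The pattern is the same as in Steps 2 and 3.

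**Step 5. Real exposure.** Now let every session carry the same event probability of 0.01 (assumed). Per-session incidence is 1% in each Tai Chi arm. The share of participants with at least one event is 1 − 0.99^12 = 11.4%, 1 − 0.99^36 = 30.4% and 1 − 0.99^60 = 45.3%. Here the higher burden at higher frequency is genuine, and the per-session figure does not show it.

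**The case against.** The strongest objection concerns direction. A reader might infer that detection bias makes the safety figures look worse as frequency rises. The protocol does not support that. Its measure is per session, and Step 3 shows it flat or falling. Even for raw counts, only one-day events rise across all three arms; from two days upward the 3- and 5-session arms are the same. This objection stands, and the point is therefore non-comparability, not upward bias.

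A reader might also infer that nurses are the sole means of detection and that control participants are never asked about harms. The text does not say so. It says nurses handle events; it does not say how every event comes to light, nor that a nurse attends every session. The schedule table is not shown, and an article may leave details of harm enquiry to the full protocol. This stands as a limit on wording: one can say only that no other route is described. It does not dispose of the point, because the article itself sets out the staff, the record, the causality judgement and the formula, and that procedure is unequal across arms.

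Other contacts exist: weekly lectures in all arms, weekly telephone calls on learning in the Tai Chi groups, and daily WeChat notices covering training plans, exercise reminders, sign-in and medicine changes. Spontaneous reports through these would narrow the differences in Step 2. None is described as a harm enquiry.

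The uniform-onset assumption also fits training injuries poorly. These would cluster in or just after sessions, where all three Tai Chi arms are observed alike, and more of them at 60 than at 12 sessions is partly real exposure. That is correct, and it confines Steps 2 to 4 to between-session events. Finally, control harms are already excluded by the definition and the denominator. That is a further reason why no control figure exists; changing those two alone would still leave capture unequal.

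**Conclusion.** The point holds in a limited form. As described, the route depends on session contact and the incidence is divided by sessions, so the group safety figures do not measure harm on a common footing. With identical true between-session harm, counts may differ up to 5-fold (5 versus 1 session per week, one-day events). Per-session incidence may range from equal down to one fifth (events lasting, or recalled for, 7 days). If harm per session is constant, the same measure conceals a real rise per participant. Control has no figure at all.

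The sizes rest on assumed onset, duration, recall and session days, and would shrink if participants report unprompted between sessions. That the figures depend on session frequency, and that control is 0/0, follows from the text. Because no formal harm comparison is planned, the consequence lies in how the descriptive safety results can be read, not in the primary analysis. It is worth correcting because it is cheap, and an enquiry missed during the trial can be replaced only by longer recall.

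**What to change.** In Safety evaluation, add one open harm item, identical in all four arms, at the existing week 4, 8, 12 and 24 assessments: any new or worse health problem since the last assessment. It should not be restricted to problems attributed to Tai Chi. Use a self-completed form, or have an unblinded research assistant ask, so that the outcome assessor stays blinded. From this source, report the number and percentage of participants with at least one event in each arm as the between-arm description. Keep the nurses' session records and the per-session incidence as a separate description of the Tai Chi arms, not set against control or across frequencies as a measure of harm. The handling of events as they occur need not change.

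The cost is one form item at four assessments that already take place, and a sentence or two in the section. The downside is recall over 4 weeks (12 weeks at week 24). Some short-lived events will be missed, but with the same enquiry and the same recall window in every arm. Participants know their allocation, so differences in willingness to report cannot be ruled out.

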#### Sample size

The sample size was estimated using the PASS software (ver. 15.0). Limited studies have focused on the effect of different weekly frequencies of TC in elders with CNLBP. As such, the primary indicator was the changes of LBP intensity at rest (represented as VAS, score of 0–10). The sample size was calculated via the minimum clinically important difference of 2 on the VAS of pain intensity, and expecting the standard deviation of 2.2 immediately following TC training [33–35]. Considering the multiple comparison, the Bonferroni adjustment was applied, a sample with 240 participants was needed with a power of 80% and an alpha of 0.05 (*α*=0.05 is the overall allowable type I error in the comparisons between each experimental group and the control group sequentially). Moreover, considering a 15% attrition rate, at least 71 participants per group will be needed in this protocol trial [Total participants: 240/ (1−0.15) ≈ 284 participants, considering an equal allocation of 1:1:1:1 to four groups].

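### The only stated adverse-event measure, AE sessions over exercise sessions with AEs limited to harm caused by Tai Chi, is undefined for control and can hide or reverse a higher per-participant burden at 5 sessions/week

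*Protocol article*

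**What the plan says.** The Safety evaluation section of the protocol article restricts the term to "AEs, defined as any impairment caused by TC training". A doctor is then to "evaluate their correlation with clinical intervention training". Incidence is calculated as "Incidence of AEs (%) = (sessions with AEs / total exercise sessions in this group) × 100", and the stated purpose is "to measure the safety concerns". The article gives no other safety summary.

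The Tai Chi arms train "one, three or five sessions/week, 60 min/session, sustain for 12 weeks". The control arm "will not receive any rehabilitation treatment during the intervention, except for one health lecture per week for 12 weeks", so it has no exercise sessions. The Sample size section states that "at least 71 participants per group will be needed in this protocol trial".

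The withdrawal criteria, under Eligibility criteria, refer to severe adverse events occurring during the study, without tying them to Tai Chi. That is a wider use of the term than the definition in Safety evaluation.

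**The concern.** The trial is meant to help clinicians choose a weekly frequency for older people with chronic back pain. That choice weighs benefit against harm per person over the whole course. The stated measure serves it poorly in four ways.

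- **Control.** With causation by Tai Chi in the definition and exercise sessions in the denominator, control has neither a possible event nor a denominator. The randomised comparator gives no AE figure.
- **Circularity.** Causation is part of the definition, yet relatedness is assessed afterwards. An event that staff do not at first attribute to Tai Chi may never reach the doctor.
- **Coverage.** The numerator counts sessions. Events between sessions or in weeks 13 to 24 have no clear place in it, and several events in one session count once.
- **Dose.** The denominator grows in direct proportion to the randomised frequency, so the rate removes the factor that the trial compares.

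This is a matter of stated text, not of detail left to an analysis plan. Events that were never recorded cannot be recovered at analysis.

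**Working it through.** The article states a formula and no AE figure, so there is no number to reproduce.

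**Inputs from the article:** 71 participants per arm; 1, 3 or 5 sessions/week for 12 weeks; no exercise sessions in control.

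**Assumptions, not in the article:** full attendance, a session counted once per participant, and the AE counts and probabilities below.

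**Denominators.** Sessions per participant = 12 × frequency = 12, 36, 60. Participant-sessions per arm = 71 × 12 = 852, 71 × 36 = 2556, 71 × 60 = 4260. Control: 71 × 0 = 0, so its figure is 0/0.

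**Case A: 10 AE sessions in each Tai Chi arm, each in a different participant.** Session rates are 10/852 = 1.17%, 10/2556 = 0.39% and 10/4260 = 0.23%. The share of participants affected is 10/71 = 14.1% in each arm.

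**Case B: constant probability p per session, sessions independent.** The expected session rate is p in every Tai Chi arm. The 12-week risk per participant is 1 − (1 − p)^(12 × frequency):

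| p | Session rate, all Tai Chi arms | Risk at 1/week | Risk at 3/week | Risk at 5/week |
|---|---|---|---|---|
| 0.2% | 0.2% | 2.4% | 7.0% | 11.3% |
| 0.5% | 0.5% | 5.8% | 16.5% | 26.0% |
| 1% | 1% | 11.4% | 30.4% | 45.3% |

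At p = 0.5%, the expected number of AE sessions is 4.3, 12.8 and 21.3. The session rate shows none of this gradient.

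**Case C: a reversal.** Take 10 AE sessions at 1/week and 20 at 5/week, each in a different participant. The session rates are 10/852 = 1.17% and 20/4260 = 0.47%, while the shares affected are 10/71 = 14.1% and 20/71 = 28.2%. The 5/week arm needs 50 AE sessions (50/4260 = 1.17%) to show the rate that 10 produce at 1/week.

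**Meaning of session.** If it means a class session, the denominators are 12, 36 and 60, and 10 AE sessions give 10/12 = 83.3%, 10/36 = 27.8% and 10/60 = 16.7%. The article does not say which meaning applies, and the choice changes the 1/week figure from 1.17% to 83.3%.

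**The case against.** AE sessions over exercise sessions is a recognisable exposure-adjusted rate with its parts openly stated. In Case A the risk per session at 5/week really is one fifth of that at 1/week, so the formula reports its own quantity correctly. This stands: the rate is legitimate as a supplement, and the fault is that it is the only measure.

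A reader might infer that the formula always shrinks as frequency rises and so makes 5/week look safest. The article does not support that. The rate falls as 1/frequency only if AE-session counts are equal across arms. Under constant per-session risk it is flat, and it rises if per-session risk rises.

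A reader might also infer that the trial will hold no safety information on control. That goes too far. Reasons for every withdrawal are recorded through follow-up, severe adverse events are a withdrawal criterion with no stated link to Tai Chi, and an independent board reviews data every 4 weeks. For recorded AEs, the case report forms hold time, duration, degree and treatment, so participant counts could probably be derived for the Tai Chi arms. None of this supplies a control AE count or a stated per-participant measure.

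Safety is not a primary or secondary outcome, and no between-arm AE test is announced. That limits the consequence, but the formula is still offered as the measure of safety for each group.

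Finally, the circularity may be loose wording: suspected events captured first and adjudicated later. That is plausible, but the definition does not say so.

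**Conclusion.** The point holds in a limited form. From the text alone, with no assumption about event rates, four things follow: no control AE can be counted and the control figure is 0/0; causation is built into the definition and then assessed; events outside sessions have no clear place in the numerator; and the denominator varies 12 : 36 : 60 per scheduled participant by design.

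The rate can therefore hide a higher per-participant burden at 5/week (Case B) or reverse it (Case C). Whether it will do so depends on event rates that the article does not give. The percentages are illustrations that assume 71 per arm, full attendance and participant-sessions; Case B also assumes independent sessions.

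The primary efficacy analysis is unaffected. The safety summary should be changed before data collection.

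**What to change.** - Define an AE as any untoward event from randomisation to week 24 in all four arms, regardless of cause, and reconcile the term with its use in the withdrawal criteria.
- Ask about AEs in the same way in every arm at existing contacts (weekly lectures during the 12 weeks, outcome visits through week 24), and record relatedness as a separate item.
- As the main safety measure, report participants with at least one AE over participants randomised in each arm, with between-arm differences and confidence intervals.
- Keep the per-session rate as a descriptive supplement for the Tai Chi arms only, and state whether a session is a participant-session or a class session.

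The cost is revised case report form wording, one table, and somewhat more AE recording. Control needs a short standard enquiry of its own: the article assigns nurses to the intervention groups and mentions none for control, and its WeChat messages are mainly task notices and reminders. The lectures and visits already provide the contact.
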